### **13.6 Overview (7/1/97)**

When the study was originally designed, a surrogate endpoint, time to second prostate-specific antigen failure, for cause specific survival was used as the primary endpoint. Zietman et. al. have reported on this surrogate endpoint using patients treated at Massachusetts General Hospital

Cancer. The statistician responsible for RTOG prostate studies was a consultant to that paper. It should be noted that 95% of the patients had T3 primaries and the remaining 5% had T4 primaries in the previous series, while only patients with T1b-T2b tumor are eligible for the current study.

Since RTOG 94-08 opened to patient entries, some information about overall survival and cause specific survival has become available from other RTOG prostate studies. Two significant findings that are relevant to this study are the cause of death and the importance of the Gleason score.

- A considerable percentage of deaths are attributable to causes other than prostate cancer. This percentage varies with T-stages and Gleason score groups. As seen in the table below, the percent of deaths attributable to prostate cancer decreases with the lower stages and/or lower Gleason groups.

### Cause of Death

| RTOG Protocol              | Median FU Years* | Gleason Groups** | Total Deaths | Prostate No. (%) | Other No. (%) | Unknown No. (%) |
|----------------------------|------------------|------------------|--------------|------------------|---------------|-----------------|
| 7706
(T1/T2)            | 9.75             | combined         | 258          | 76(29%)          | 165(64%)      | 17(7%)          |
|                            | 10.23            | 2-6              | 186          | 49(26%)          | 123(66%)      | 14(8%)          |
|                            | 7.69             | 7-10             | 62           | 25(40%)          | 34(55%)       | 3(5%)           |
| 8531+8610
(T3, RT only) | 4.51             | combined         | 159          | 75(47%)          | 73(46%)       | 11(7%)          |
|                            | 4.93             | 2-6              | 27           | 8(30%)           | 18(67%)       | 1(3%)           |
|                            | 4.44             | 7-10             | 127          | 67(53%)          | 52(41%)       | 8(6%)           |

\* for all eligible patients in the study

\*\* centrally reviewed

- The positive prostate study RTOG 85-31 showed that adjuvant hormonal arm is significantly better than the control arm in all disease related endpoints such as local control and disease free survival. However, survival benefit was only demonstrated in a group of patients with centrally reviewed Gleason scores 8-10.

One implication of these findings, which will be illustrated further later, is that a significant difference in absolute survival may be practically unattainable unless the treatment effect in disease specific survival is large. With this new information, the RTOG statistical unit felt that the protocol should be amended to incorporate these findings. In general, if neoadjuvant TAS is successful, there should be positive impact on disease specific survival. Thus, we modified the study to use disease specific survival as the primary endpoint with a median of 10 years follow-up, while the overall survival is considered as a secondary endpoint for the study. We also acknowledge that Gleason score is a significant risk factor and must be included in the design.

Other studies have shown a high rate of recurrence free survival for patients whose pre-treatment PSA was less than 4. We decided not to utilize this information in the sample size calculation because there are no long term results available in men with PSA less than 4. Furthermore, almost all published studies showed a high correlation between pre-treatment PSA and Gleason score.

## 13.7 Study Endpoints (7/1/97) (7/14/08)

The primary endpoint for this trial is overall survival, on which the sample size is calculated (See Section 11.3.10 for the definition). The absolute survival with failure of death from all

15

causes is a secondary endpoint. We also consider the time to second PSA failure defined in Section 11.3.7 as a secondary endpoint for the trial. The collection of these data allows us to examine the hypothesis that the second PSA failure is a surrogate for death from prostate cancer. With an adequate long period of follow-up, we should be able to study the relationship among these times to endpoints.

## **13.8 Sample Size Determination (7/1/97)**

### **13.8.1 Assumptions**

1. The long-term follow-up results of a similar patient population treated by RT alone are available from RTOG 77-06. The figures (a) and (b) show a smoothed estimate of yearly hazard for patients with Gleason score 2-6 and Gleason score 7-10, respectively. These estimates will be used as the yearly hazards for the control arm in the sample size calculation. From the figures, we may notice that for patients with Gleason score 2-6 the hazard of death from all causes is 3-4 times as high as the hazard of death from prostate cancer; and for patients with Gleason 7-10 this ratio is about 2.

Figure A

[figure not shown]

Figure B

[figure not shown]

2. As of November 1996, 440 patients with pre-treatment data available have been entered into RTOG 94-08. Excluding ineligible patients and eligible patients without institutional Gleason scores, we estimate that 36% of the patients have Gleason scores of 7-10. (*As of May 1, 1997, this percentage is 38% with 622 patients having completed the initial evaluation.*)
3. To determine a reasonable estimate of the effect of neoadjuvant regimen, we have looked at a subpopulation of RTOG 8531 in which the patients mostly met the eligibility criteria of RTOG 9408 except for the criteria of the nodal involvement. We feel that the selected population may provide some insight about the population of RTOG 94-08 and its treatment effect. With 33 and 76 patients in Gleason 2-6 and Gleason 7-10 groups respectively, we calculated the effectiveness of RT plus immediate hormone assuming constant hazard. The following table lists hazard reduction in comparison to the control arm in overall survival and disease specific survival. Since only 5 years of follow up are available for RTOG 85-31 and few death

cases have been observed in patients with Gleason 2-6, only the estimated hazard reductions for the group of patients with Gleason 7-10 tumors can be used.

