## 13.4 Analysis Plan (11/13/00) (11/17/05) (7/14/08)

Analyses of time to treatment failure will use the log-rank test and the Cox proportional hazards model. All hypothesis testing will be two-sided. Exploration of the effects of pretreatment prognostic factors such as stage, Gleason score and PSA will be done using the Cox proportional hazards model. There will also be exploratory analyses of the different reasons for treatment failure.

Interim accrual and morbidity reports will be done at least semi-annually prior to the RTOG group meeting. The report will describe accrual by institution and project completion of accrual. It will give the distribution of pretreatment characteristics and a tabulation of toxicities.

Three interim treatment comparisons shall be performed when we observe 29%, 60% and 80% of the 261 required maximum number of prostate cancer related deaths. The first interim analysis is projected to take place at the second year after the closure (*every patient has at least one year of follow-up*). The second and third interim analyses are projected to take place at the fifth year (*4 years of follow-up*) and seventh year (*6 years of follow-up*) after the closure, respectively. For each of these interim analyses, toxicity, treatment delivery and efficacy statistics will be reported to RTOG DMC. The boundary for early stopping (*or the nominal significance level for the test*) will be computed based on the observed number of deaths according to the O'Brien-Fleming alpha spending function approach. If the difference is highly significant, i.e., p value less than the

nominal level, the responsible statistician will recommend to DMC that the study be written up for publication.

Analysis of SAQ will be performed on all patients that complete baseline questionnaires. The analysis will utilize analysis of variance, and repeated measures analysis of variance to examine differences in treatments. SAQ will be examined for responsiveness in follow-up and correlation to changes in serum testosterone. Analysis of SAQ by subgroups will be undertaken for groups with sufficient sample size.

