The study was designed for three interim analyses of the primary endpoint, disease-specific survival (death due to prostate cancer) when we observe 29% (76), 60% (157) and 80% (209) of the 260 required maximum number of prostate cancer related deaths. D'Amico et al showed a statistically significant improvement in disease-specific survival with six months of total androgen blockade given two months before, during and after radiation therapy in a similar patient population. Based on this result, the disease site and study chairs requested an early look at disease-specific survival. This request was presented at the RTOG Data Monitoring Committee (DMC) in June 2005. The RTOG DMC approved an early analysis of the primary endpoint. Thus the first interim analysis is now planned to be done with 66 deaths. The boundary for early stopping (or the nominal significance level for the test) will be a modified Haybittle-Peto boundary. The stopping boundary of each of the three interim analyses is 3.291 (for a nominal significance level of 0.001) and the boundary for the final analysis is 1.96 which makes the overall significance level 0.051.

**All eligible patients who are randomized to the study will be included in the comparison of treatment arms (intent-to-treat analysis).**

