### 13.8.2 Sample Size

For the primary endpoint, disease specific survival, we will use a two-sided log-rank test to detect the treatment effect of 33% reduction in hazard of death from prostate cancer with a significance level of 0.05 and a power of 90%. Using Lakatos' method (*assuming there is no drop-in and noncompliance, and loss of follow-up rate equals to the other cause mortality rate*), a total of 1779 patients is required to be accrued uniformly over five years and followed for additional eight years before the final analysis. Accounting for possible 10% unevaluable cases, **the total required sample size is 1980 for both arms of the study.**

With the proposed sample size, we will be able to detect a 16.7% average reduction in hazard of death from all causes with 75% power. (*However, if the reduction in death from all causes is 11%, a formidably large sample size will be required*).

If the current percentage (36%) of patients with Gleason 7-10 holds for the study, we will expect to enter 640 such evaluable patients. With this expected number of patients, we will be able to detect a 40% reduction in hazard of death from prostate cancer for patients with Gleason 7-10 with a statistical power of 80%. On the other hand, we will be able to detect a 20% reduction in hazard of absolute survival with statistical power of 53% for patients with Gleason 7-10.

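### Section 13.8.2 states 90% and 80% disease-specific power without the event counts they need, although the 2005 text points to fewer prostate-cancer deaths than projected and the 716-death trigger does not secure 261

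*Protocol*

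**What the plan says.** Section 13.8.1 (dated 7/1/97) uses smoothed RTOG 77-06 hazards by Gleason group: "These estimates will be used as the yearly hazards for the control arm in the sample size calculation". Section 13.8.2 says of disease-specific survival "we will use a two-sided log-rank test" and sets the target as a "33% reduction in hazard of death from prostate cancer with a significance level of 0.05 and a power of 90" per cent. On size and timing it says "a total of 1779 patients is required to be accrued uniformly over five years and followed for additional eight years before the final analysis". For the subgroup it says "we will be able to detect a 40% reduction in hazard of death from prostate cancer for patients with Gleason 7-10", with 80% power in 640 evaluable men.

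Section 13.4 ties three looks to 29%, 60% and 80% of 261 prostate-cancer deaths (76, 157 and 209). On timing, "The first interim analysis is projected to take place at the second year after the closure"; the other two are projected for the fifth and seventh years. The 2005 text of 13.4 records that an early look was presented to the data monitoring committee in June 2005 and approved: "Thus the first interim analysis is now planned to be done with 66 deaths".

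Since 7/14/08 overall survival has been primary (13.2.1, 13.7) and the final analysis takes place at 716 deaths from any cause (13.4.1). Disease-specific survival is secondary but still tested at 0.025 (13.4.2). Section 13.8.2 was not revised: it still calls disease-specific survival primary and still states the 1997 powers.

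**The concern.** A power stated for a fixed follow-up period is only as good as the event rate behind it. Here the protocol itself carries a sign that the rate was too high. A look planned for 76 deaths is brought forward to 66 only if 76 have not yet been reached, and by the 13.4 timetable 76 should have been reached in the second year after closure. Nothing in the later text revisits the hazards or the powers. The 2008 change of trigger adds a second gap, because no current passage makes the final analysis wait for 261 prostate-cancer deaths.

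At stake is how a null disease-specific result is read. Taken from 13.8.2, it would count as a negative finding with 90% power, when the true power may be well below that.

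**Working it through.** **1. The stated powers reproduce.** For a log-rank test with equal arms (Schoenfeld), power = Φ(½·√d·|ln HR| − 1.96), where d is the number of prostate-cancer deaths.

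- All patients, HR 0.67 (|ln HR| = 0.4005), d = 261: ½ × 16.155 × 0.4005 − 1.96 = 1.275, so power is 89.9%. Stated: 90%.
- Gleason 7-10, HR 0.60 (|ln HR| = 0.5108), 80% power: d = 4 × (1.960 + 0.842)² / 0.5108² ≈ 120.
- 0.36 × 1779 = 640, and 1779 / 0.9 = 1977 against the stated 1980 ("Accounting for possible 10% unevaluable cases").

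So the powers are conditional on about 261 and about 120 deaths. Figures A and B are not shown, so the 1779 cannot be rebuilt from the hazards.

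**2. Closure date (assumption).** Section 13.8.1 gives 440 men at November 1996 and 622 at 1 May 1997: 182 in six months, or 364 a year. (1980 − 622) / 364 = 3.73 years, so 1980 is reached about January 2001, some 4.3 years before June 2005. This agrees with five-year accrual and with an eligibility checklist dated 11/13/00, but the document does not state it.

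**3. Projected against implied deaths in mid-2005.** Section 13.4 pairs the second year after closure with at least one year of follow-up, so its timetable has two readings:

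- Reading A: 76, 157 and 209 deaths at years 2, 5 and 7 after closure, and 261 at year 8.
- Reading B: the three looks a year earlier (years 1, 4 and 6), with 261 still at year 8.

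I interpolate linearly, take the ratio of implied to projected deaths, and apply it to 261. The count used is 66, or 75 as the most that stays below 76.

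| Closure before look | Reading | Projected | Count | Ratio | Deaths at year 8 | Power, HR 0.67 |
|---|---|---|---|---|---|---|
| 4.3 years | A | 138 | 66 | 0.48 | 125 | 61% |
| 4.3 years | A | 138 | 75 | 0.54 | 142 | 66% |
| 4.3 years | B | 165 | 66 | 0.40 | 104 | 53% |
| 4.3 years | B | 165 | 75 | 0.45 | 119 | 59% |
| 3 years | A | 103 | 66 | 0.64 | 167 | 74% |
| 3 years | B | 130 | 66 | 0.51 | 132 | 63% |
| 2 years | A | 76 | 66 | 0.87 | 227 | 85% |
| 2 years | B | 103 | 66 | 0.64 | 167 | 74% |

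**4. Cross-check with a competing-risk model.** The model assumes uniform accrual over 5-6 years, an other-cause hazard of 0.031-0.045 a year, and a Weibull prostate-cancer hazard scaled to 261 deaths at year 8. The 13.4 timetable needs a rising hazard (shape 1.8-2.1).

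- 66 deaths at 4.0-4.6 years: hazard 0.44-0.52 of design, 121-143 deaths at year 8, power 60-67%.
- 75 deaths at 4.3 years: about 0.54 of design, power 68-69%.
- 66 deaths at 3 years: power 76-78%. At 2 years: 87-88%.
- A constant hazard with 66 deaths at 4.3 years gives 48-50%, but does not fit the 13.4 timetable.

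A larger true effect does not explain the gap: moving from HR 0.67 to HR 0.50 changes pooled deaths by a factor of about 1.50 / 1.67 = 0.90.

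**5. Power at the trigger now in force (716 deaths from any cause).** This uses RTOG 77-06's own share of deaths due to prostate cancer.

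- 29% (table in 13.6): 0.29 × 716 = 208 deaths, power 82%.
- 14/46 (13.3): 0.304 × 716 = 218 deaths, power 84%.
- Prostate plus all unknown-cause deaths, (76 + 17) / 258: 0.360 × 716 = 258 deaths, power 90%.

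This step needs no closure date and assumes no shortfall.

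**The case against.** The strongest counter-arguments are these.

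- **66 is not a dated count.** It is a planned look size with no data cut-off, and it is also 25% of 261 rounded up (65.25). This stands. What survives is the weaker inference that 76 had not been reached, which is why 75 is carried through the table.
- **Closure is inferred from one six-month interval, and the two accrual counts are worded differently.** This stands and drives the width of the range. For no shortfall on reading A, closure would have to be about mid-2003, which means about 1358 / 6.17 = 220 men a year after May 1997, some 40% below the documented pace. The document does not exclude that.
- **The looks are event-driven, so a lower hazard only delays 261 deaths.** This is true of the monitoring plan as designed. It does not rescue the stated power, because 13.8.2 ties it to eight years of follow-up and the only final trigger now in force is 716 deaths from any cause.
- **The endpoint is now secondary and the 1997 calculation was sound when made.** Both are correct. The overall-survival power in 13.4.1 is untouched, and this is not an arithmetic error. The complaint is that a superseded power is left standing as current.

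A reader might go further and infer that the RTOG 77-06 hazards are twice too high, that disease-specific power is about 50-65%, and that Gleason 7-10 power is about 40-52%. The document does not support that. The hazard curves are not visible, the factor of two depends on the assumed closure date, and no death count by Gleason group appears anywhere, so a subgroup figure would need an unsupported assumption of a proportional shortfall.

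**Conclusion.** The concern holds in a limited form. The 90% and 80% in 13.8.2 are correct only at about 261 and about 120 prostate-cancer deaths, and the current protocol secures neither number.

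- **At eight years after closure:** about 53-69% power for a 33% reduction if accrual closed about early 2001 and between 66 and 75 prostate-cancer deaths had occurred by mid-2005. If closure was only two to three years before the look, about 63-88% with 66 deaths; with 75 deaths at two years on reading A there is almost no shortfall. The direction is well supported; the size is not fixed by the document.
- **At 716 deaths from any cause:** about 82-84% on RTOG 77-06's own prostate-cancer share, and about 90% only if every unknown-cause death is counted. This assumes that the RTOG 77-06 share carries over to this trial.
- **Gleason 7-10:** no shortfall can be derived.

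The primary overall-survival analysis is not affected.

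**What to change.** 1. In 13.8.2, mark the disease-specific powers as the 1997 design for a superseded primary endpoint, conditional on about 261 prostate-cancer deaths (all patients) and about 120 (Gleason 7-10).
2. Restate the expected number of prostate-cancer deaths, and the disease-specific power, at the 716-death analysis, using the pooled (arm-blind) prostate-cancer death rate from this trial.
3. In 13.4, correct or remove the projected calendar times of the looks.

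The cost is protocol wording and one recalculation from pooled event counts. No more patients and no change to the primary analysis are needed. The price is that the stated power for the secondary endpoint becomes less favourable.

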## Estimated Hazard reduction in RTOG 8531

|                                 | Gleason
2-6 | Gleason
7-10 |
|---------------------------------|----------------|-----------------|
| Overall
survival             | 8%             | 32%             |
| Disease
specific
survival | NA             | 48%             |

We realize that because of the nodal involvement criteria of RTOG 8531, the selected sub-population includes less favorable patients than those in RTOG 94-08. Regardless of Gleason score groups, we would expect a hazard reduction in death from prostate cancer due to neoadjuvant hormone regimen to be less than 50%. Thus, we hypothesized a 33% hazard reduction in death from prostate cancer due to hormone treatment.

Based on the estimates of RTOG 77-06 given in assumption 1, we can translate the hazard reduction in disease specific survival into the hazard reduction in absolute survival. A 33% reduction in death from prostate cancer corresponds to an average of 11% reduction in death from all causes.

### 13.8.2 Sample Size

For the primary endpoint, disease specific survival, we will use a two-sided log-rank test to detect the treatment effect of 33% reduction in hazard of death from prostate cancer with a significance level of 0.05 and a power of 90%. Using Lakatos' method (*assuming there is no drop-in and noncompliance, and loss of follow-up rate equals to the other cause mortality rate*), a total of 1779 patients is required to be accrued uniformly over five years and followed for additional eight years before the final analysis. Accounting for possible 10% unevaluable cases, **the total required sample size is 1980 for both arms of the study.**

With the proposed sample size, we will be able to detect a 16.7% average reduction in hazard of death from all causes with 75% power. (*However, if the reduction in death from all causes is 11%, a formidably large sample size will be required*).

If the current percentage (36%) of patients with Gleason 7-10 holds for the study, we will expect to enter 640 such evaluable patients. With this expected number of patients, we will be able to detect a 40% reduction in hazard of death from prostate cancer for patients with Gleason 7-10 with a statistical power of 80%. On the other hand, we will be able to detect a 20% reduction in hazard of absolute survival with statistical power of 53% for patients with Gleason 7-10.

**\* Added 4/5/96**

**\*\* Added 7/1/97**

**\*\*\* Added 7/14/08**

## APPENDIX II

### **KARNOFSKY PERFORMANCE SCALE**

|     |                                                                              |
|-----|------------------------------------------------------------------------------|
| 100 | Normal; no complaints; no evidence of disease                                |
| 90  | Able to carry on normal activity; minor signs or symptoms of disease         |
| 80  | Normal activity with effort; some sign or symptoms of disease                |
| 70  | Cares for self; unable to carry on normal activity or do active work         |
| 60  | Requires occasional assistance, but is able to care for most personal needs  |
| 50  | Requires considerable assistance and frequent medical care                   |
| 40  | Disabled; requires special care and assistance                               |
| 30  | Severely disabled; hospitalization is indicated, although death not imminent |
| 20  | Very sick; hospitalization necessary; active support treatment is necessary  |
| 10  | Moribund; fatal processes progressing rapidly                                |
| 0   | Dead                                                                         |

